## Abstract

**Background:**

Intimate Partner Violence (IPV) is a well-established driver of mental health problems, often doubling the prevalence of depression. In Nepal, approximately one in four women experience IPV, with young women disproportionately affected by mental health issues. Many women in Nepal reside with their mothers-in-law (MILs), who can influence violence and restrict women’s mobility, highlighting the importance of including them in interventions targeting IPV. To address this, we developed a Multi-component family Intervention to Lower depression and Address intimate Partner violence (MILAP) and will conduct a randomized controlled trial (RCT) to evaluate its effectiveness in reducing IPV and depression.

**Methods:**

This RCT will enroll 300 family triads, each comprising of a young married woman (aged 15–24), her husband, and her MIL. Blinded staff will conduct baseline assessments, after which each triad will be randomly assigned to either the MILAP or Enhanced Usual Care (EUC). MILAP comprises nine sessions delivered by trained psychosocial counselors and focuses on strengthening the supportive relationship between MILs and daughters-in-law (DILs), providing behavioral couples therapy, and enhancing overall family dynamics. EUC includes standard care, such as individual and group counseling for IPV, enhanced with crisis counseling and referral support to ensure participant safety and access to additional resources. All participants, regardless of intervention allocation, will be assessed at baseline and at 1, 3, 6, 9, and 12-month follow-ups. These assessments will measure: primary outcomes [depression using Patient Health Questionnaire-9; IPV using Indian Family Violence and Control Scale], secondary outcome [post-traumatic stress disorder (PTSD) using PTSD CheckList-Civilian Version], and other outcomes. We will also conduct serial in-depth interviews to explore the mechanisms underlying MILAP’s effectiveness and perform a cost-effectiveness analysis to assess its potential for scalable implementation.

**Discussion:**

MILAP is a culturally adapted, family-based intervention designed to reduce IPV and depression among young Nepali women by improving communication, strengthening coping skills, and fostering supportive family relationships. This trial will assess MILAP’s effectiveness, ethical rigor, cultural relevance, and scalability, with the goal of reducing IPV and improving family dynamics in low- and middle-income settings.

**Trial registration::**

This trial is registered in ClinicalTrials.gov with the National Clinical Trial (NCT) number: NCT06834867; first registered on February 24, 2025.

## Introduction

### Background and rationale {6a}

Intimate partner violence (IPV) and mental health problems pose major global public health challenges, particularly in low- and middle-income countries (LMICs), where one in three women experiences IPV.(1–4) IPV is defined as abusive control or psychological, physical, and sexual violence perpetrated by an intimate partner.(3) It is a well-established contributor to mental health problems, often doubling the prevalence of depression, increasing social isolation, and escalating the risk of post-traumatic stress disorder (PTSD).(5–12) In South Asia, 25–50% of women who experience IPV report depressive symptoms.(13–16) In Nepal, our study site, IPV affects 26% of women.(17) Despite ongoing IPV, young women in LMICs are often unable or unwilling to pursue divorce or separation.(18, 19) Young women in Nepal face heightened vulnerability, with half marrying before the age of 18 (20) and experiencing disproportionately high rates of mental health issues. Among women of reproductive age, suicide is the leading cause of death. (20–24)

There is evidence that persistent IPV perpetuates mental health problems, severely hinders recovery, and heightens suicide risk.(7, 25–27) Existing interventions addressing IPV and mental health issues in LMICs are scarce and often ineffective.(28–31) Currently available interventions, such as cognitive behavioral therapy, have shown effectiveness primarily among women who have already exited relationships that led to IPV (32–34) but may be less effective for those who remain in such relationships and continue to experience violence. Therefore, there is an urgent need for culturally appropriate, evidence-based interventions that simultaneously reduce IPV and improve mental health.

Family-based interventions offer a promising approach in LMICs, where IPV and mental health issues often extend beyond spousal relationships, as many married women in LMICs reside in households with in-laws, and mothers-in-law (MILs) often influence IPV and restrict the freedom of movement (FOM) of daughters-in-law (DILs).(1, 35, 36) Our prior study found that positive MIL-DIL relationships can enhance spousal and family dynamics, and improve women’s (DILs’) mental health. (37) Despite this, most interventions focus solely on women (38–42), occasionally involve husbands (16, 43–49), but often overlook the broader family context. Such interventions may unintentionally place the burden of change on women, rather than creating a supportive home environment where they can access support from their MILs. Furthermore, if women access IPV services independently, it may escalate IPV if perpetrators become aware. In addition, many women might hesitate or avoid participating in IPV interventions due to the stigma associated with disclosing IPV, fear that disclosure may worsen the violence, and a desire to maintain and protect the family unit and honor. (50–53) Moreover, men who engage in IPV often normalize their behavior and may be less receptive of any intervention explicitly presented as targeting IPV. Given these sociocultural circumstances, it is essential to incorporate MILs into intervention strategies and focus on a non-stigmatizing approach that promotes communication and relationship-strengthening skills within the family.(16, 44, 46–49)

To address these gaps and the need for culturally appropriate family-based interventions, we developed the **Multi-component family Intervention to Lower depression and Address intimate Partner violence (MILAP) among young married women aged 15–24 years**. MILAP **(“MEE-lahp”) means** “unity and reconciliation” in Nepali, and is a **nine-week family-based intervention**involving the young married woman, her husband and her MIL. It consists of **four combined MIL-DIL sessions for the woman and her MIL focusing on gender norms, allyship and FOM, four sessions of behavioral couples therapy (BCT)**for the woman and her husband, and **one triad summary session** involving all three family members (woman, husband, and MIL).

MILAP is informed by Social Cognitive Theory (SCT) (54–57) and findings from our pilot studies (Figure 1). SCT offers a culturally appropriate model that emphasizes interpersonal dynamics, the role of family environments in shaping behavior, and strategies to reduce barriers while enhancing facilitators of healthy behavior change.(55, 58) As women in the study setting have fewer options to leave their marriage (19), are heavily affected by the views and behaviors of their family members (37), and are committed to staying married, SCT allows us to incorporate these factors at the women’s individual, interpersonal and family levels. Given that IPV contributes to depression through mechanisms such as social isolation, restricted mobility, diminished self-efficacy and negative family dynamics, MILAP specifically targets determinants identified as modifiable in our prior research.(6–12, 59). Evidence supports the integration of IPV and mental health interventions that build problem-solving skills (60), strengthen relationships with key family members (61, 62), promote social support (63), and enhance resilience and empowerment.(64) MILAP addresses IPV and depression in a non-stigmatizing and depersonalized manner, and offers coping skills for women, mutual empowerment of MILs and daughters-in-law (DILs), and enhanced spousal communication and trust.

We conducted two single-arm pilot studies to test the acceptability, feasibility, and preliminary impact of MILAP, and found it to be well-accepted and effective in addressing IPV, depression and PTSD among young married women.(65, 66) In this manuscript, we report the protocol for a community-based fully-powered two-arm randomized controlled trial involving 300 families to evaluate the effectiveness of MILAP in reducing IPV, and improving depression and PTSD symptoms among **young married women aged 15–24**. Moreover, this randomized controlled trial will include cost-effectiveness analyses to evaluate the health and economic benefits of investing in MILAP, thereby assisting policymakers and payors in assessing MILAP’s potential for future scalability.

### Objectives {7}

The primary objective of this study is to evaluate the effectiveness of our novel family-based intervention MILAP on IPV, depression and PTSD among young married women aged 15–24 compared to those receiving enhanced usual care (EUC). To acheive this objective, we have defined three specific aims:
Conduct a 12-month randomized controlled trial to assess the effectiveness of MILAP on IPV, depression and PTSD among young married women aged 15–24 in Nepal.Conduct a mixed-methods assessment of mechanisms of change for MILAP’s effectiveness.Conduct a cost-effectiveness analysis of MILAP for IPV and depression.

### Trial design {8}

This is a community-based, randomized controlled trial in which family triads (comprising the woman, husband, and MIL) will be randomized 1:1 to either the intervention (MILAP; n=150 triads) or the comparison (EUC; n=150 triads) group.

## Methods: Participants, interventions and outcomes

### Study setting {9}

We are conducting this study in three districts of Nepal: Sunsari and Udayapur districts of Koshi province, and Sarlahi district of Madhesh province. We selected these sites because of their relatively higher prevalence of IPV (17, 67), and the existing networks and footprint of Women’s Rehabilitation Center (WOREC), which is a national non-profit organization focused on violence against women and children. This study will leverage WOREC’s networks for participant recruitment. We have obtained approvals from the Institutional Review Board of the University of California San Francisco [23–40311] and the Ethical Review Board of the Nepal Health Research Council [120–2024] to conduct this trial in these study sites.

### Eligibility criteria {10}

We will assess the eligibility of participant using the following inclusion and exclusion criteria.

#### Inclusion criteria

Married woman aged 15–24 years, living with her husband and MIL.Living in the catchment area with no stated intention of leaving during the study period.Participant speaking Maithili or Nepali language, as these two are the most common languages spoken in the study sites.Wife reporting IPV (physical, sexual or abusive control) in the last 12 months assessed by three questions from the International Violence Against Women Survey (IVAWS). (68)Wife expressing desire to remain in the current relationship/family.

#### Exclusion criteria

Any participant with severe alcohol dependence defined by the Severity of Alcohol Dependence Questionnaire (SADQ) score ≥ 31.(69) Any participant with mild to moderate dependence will be referred but not excluded.History of IPV severe enough to result in hospitalization in the past 12 months, as MILAP is not designed to address severe levels of violence. Any participant reporting severe IPV cases requiring hospitalization will be referred to tertiary care facilities.Any participant with severe depression, defined by the Patient Health Questionnaire-9 (PHQ-9) score>19 and/or high suicide risk assessed by ninth question of the PHQ-9 (“thoughts that you would be better off dead or thoughts of hurting yourself in some way”) (70) and the Nepal Emergency Suicide Screener-3 (NESS-3) adapted from the Ask Suicide-Screening Questions(71), will be referred to specialized mental health centers for assessment. After discharge from the healthcare facility, they will be approached again for eligibility.Woman who is pregnant; since pregnancy changes the family dynamics and in our study settings, pregnant woman often temporarily moves back to live with their parents where the source of IPV is no longer around. However, if any participant becomes pregnant during the study, she will continue in the study.Cognitive problems/disability precluding participation as self-reported by participant.

### Who will take informed consent? {26a}

Research assistants, trained in research ethics, will screen young women based on the inclusion and exclusion criteria outlined above. Once a woman is confirmed to be eligible and provides informed consent, the research assistant will proceed to screen her husband and MIL. The research assistant will then obtain written informed consent individually from the woman, her husband and MIL.

### Additional consent provisions for collection and use of participant data and biological specimens {26b}

In addition to providing consent to participate in the study, the consent form includes an option for participants to opt in to participate in serial in-depth interviews if invited.

We will not collect any biological samples from the study participants.

### Interventions

#### Explanation for the choice of comparators {6b}

**MILAP** is an innovative family-based intervention involving married woman, her husband, and MIL. Spanning nine weeks (11 total hours), MILAP addresses women’s current experiences of IPV and mental health needs by incorporating communication skills, stress management techniques, and strategies to strengthen relationships. We will compare MILAP with currently available IPV services, i.e., EUC delivered by WOREC. EUC builds on standard individual and group counseling by adding crisis counseling and streamlined referral mechanisms to ensure participants’ safety and facilitate access to comprehensive medical and psychosocial support.

As this is a 1:1 randomized trial, half of the total study participants (150 family triads; 450 individuals) will receive MILAP, while the remaining half will receive EUC.

#### Intervention description {11a}

##### Multi component family Intervention to Lower depression and Address Intimate Partner violence (MILAP):

The MILAP, summarized in Table 1 below, includes nine sessions delivered over nine weeks to young women aged 15–24, their husbands, and MILs.

All sessions will be delivered by counselors who have completed at least six months of psychosocial training and received specialized training to deliver MILAP from master’s-level psychologists and senior researchers. The sessions will take place in community-based counseling centers operated by either WOREC or local government, depending on participant convenience. MILAP is divided into three sections: MIL-DIL sessions, BCT sessions, and a triad summary session.

#### MIL-DIL sessions

MILAP begins with the MIL-DIL sessions for MIL-DIL dyad. The first two sessions (four total hours) are grounded in participatory learning and action principles using stories, role-plays, and discussions to enhance knowledge, skills, and social support. The primary focus of these two sessions will be to: a) discuss the impact of cultural gender norms, roles, and expectations; b) raise awareness about the negative impact of IPV on the family unit; c) establish allyship between MIL and DIL; and d) promote DIL’s empowerment and MIL’s support to improve the FOM of DILs.(72) These sessions also prepare participants for two one-hour sessions on brief behavioral activation (BA), an evidence-based technique for addressing and preventing depression.(73, 74) The BA sessionsfocus on enhancing women’s FOM and involve the MIL-DIL dyad in planning and engaging in rewarding activities,and providing positive reinforcement for DIL to experience positive feelings.

#### BCT sessions

After the completion of the MIL-DIL sessions, the husband-wife dyad will receive four weekly sessions of BCT (four total hours). The first two sessions focus on identifying shared challenges, committing to safety and trust, learning stress-coping strategies, and improving communication.(75) The third session introduces an activity to encourage caring behaviors between partners. The fourth session builds on communication skills by introducing active listening techniques and reviewing strategies learned in previous sessions.

#### Triad summary session

After completing the BCT sessions, the triad (woman, husband, and MIL) will participate in a one-hour summary session. This session will review key lessons from all previous sessions and prepare participants to address potential challenges in sustaining improvements in IPV and mental health.

Each session will incorporate role-plays, culturally grounded storytelling and reflections, regional and local folk songs, and will conclude with take-home assignments for participants to practice between sessions.

##### Enhanced usual care (EUC):

EUC will be delivered by a separate team of counselors who have completed at least six months of psychosocial training but have not received specialized MILAP training, in order to avoid potential contamination. These counselors will conduct an initial safety assessment and offer: a) WOREC’s IPV rehabilitation services, which include access to a women’s shelter, safety and protection from the perpetrator, mental health counseling, legal support, and health services; b) educational materials on safety planning, the consequences of ongoing IPV, written resources for reducing IPV, and information about a nationwide IPV/DV hotline; c) referrals to wraparound services based on the woman’s needs and priorities, including legal support, safe housing, psychosocial counseling, health services, and livelihood support; d) referral to a one-stop IPV center, along with information about available options, including support for leaving the relationship if the participant expresses that desire.

Since this study includes women currently experiencing IPV, we will enhance the usual care by adding two key services: mental health crisis counseling and a referral pathway for those in need of specialized support.

**Crisis counseling** will be provided to all participants, regardless of their intervention allocation, who are identified as being at high suicidality risk, as assessed by the study team members using the trigger (ninth) question of the PHQ-9 (“thoughts that you would be better off dead or thoughts of hurting yourself in some way”) and three questions from the NESS-3 that assess imminent suicide risk. Contracted crisis counselors will deliver these services, assess participants’ immediate risk, and provide urgent support as needed. If further care is required, study team members will facilitate referrals to tertiary care facilities. In cases where participants report escalated violence requiring immediate intervention, they will be referred to the One-Stop Crisis Management Center (OCMC) in their respective district. OCMC is a hospital-based center that provides a comprehensive range of services for survivors of gender-based violence, including medical services, psychosocial counseling, legal aid, personal security, rehabilitation and vocational training, coordination with safe homes, and connections to local community-based organizations working in the area of IPV.(76) If a woman doesn’t feel safe or doesn’t wish to return, study team members will connect her with WOREC for access to safe shelter or housing services.

#### Criteria for discontinuing or modifying allocated interventions {11b}

Participation in this trial will be voluntary and participants can discontinue at any time for any reason. Additionally, we will discontinue participants who are lost to follow-up due to various reasons, including relocation outside the study area or when the family triad no longer resides in the same household. Participants will be considered lost to follow-up if multiple contact attempts fail. These attempts include three consecutive phone calls (Days 1–3), two additional calls on alternate days (Days 5 and 7), attempts to contact to the woman’s listed emergency person (Days 8–10) and a confidential household visit to ensure participant’s well-being. If a missed assessment is found to be due to escalated violence or increased suicidality risk, we will follow established safety protocols and provide crisis management and referrals as needed.

We will not modify intervention allocation during the trial period. However, upon completion of the trial, we will offer and provide MILAP to interested EUC participants.

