#### Methods in analysis to handle protocol non-adherence and any statistical methods to handle missing data {20c}

The scenarios that are not covered by the trial protocol or those that require deviation from the protocol will be discussed within the team and will proceed with the approval of the principal investigators (PIs). We will document all such scenarios and decisions.

We will employ multiple imputation methods if missingness can be assumed to be (completely) at random for the primary analyses.(88) Alternatively, and depending on the type of analysis at hand (e.g. structural equation model), we will use full information maximum likelihood estimation.(89)

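### The discontinuation section leaves open whether reachable women who relocate or leave the household are still assessed, so primary outcomes may be missing for reasons tied to violence and possibly to arm

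*Protocol article*

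**What the plan says.** All references are to the protocol article.

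- **Criteria for discontinuing or modifying allocated interventions {11b}.** People counted as lost to follow-up are discontinued, and the examples of reasons are given as "including relocation outside the study area or when the family triad no longer resides in the same household". The next sentence sets the test for being lost: "Participants will be considered lost to follow-up if multiple contact attempts fail". It then sets out a sequence of calls, an emergency contact and a household visit. The heading concerns interventions, but the sentence discontinues participants.
- **Participant timeline {13}.** Follow-up at 1, 3, 6, 9 and 12 months is planned for everyone in both arms.
- **Statistical methods {20a}.** The main analysis is intention-to-treat at 12 months, with a longitudinal random-intercept model in addition.
- **Missing data {20c}.** "We will employ multiple imputation methods if missingness can be assumed to be (completely) at random for the primary analyses". Full information maximum likelihood is the stated alternative, depending on the type of analysis.
- **Enhanced usual care, under Intervention description {11a}.** EUC offers shelter, safe housing and information on options, "including support for leaving the relationship if the participant expresses that desire". The crisis paragraph that follows offers shelter or housing to a woman who feels unsafe or does not want to go back, without limiting this to one arm.
- **Exclusion criteria {10}.** Pregnancy at entry is excluded because a "pregnant woman often temporarily moves back to live with their parents where the source of IPV is no longer around". For a woman who conceives after enrolment the rule is different: "if any participant becomes pregnant during the study, she will continue in the study".

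**The concern.** Two adjacent sentences in {11b} give different tests. Under the first, relocation or the end of shared residence is a reason for discontinuation. Under the second, a woman is lost only when she cannot be contacted. A woman who has left the household but answers her phone can be classed either way, and staff who follow the first sentence could stop assessing her.

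Leaving the household happens after randomisation and is closely tied to both primary outcomes, depression (PHQ-9 above 9) and IPV (IFVCS score). It can follow escalating violence, and it changes later exposure to violence. The trial's own services can also bring it about. If reachable women stop being assessed when they leave, their 12-month outcomes are missing for reasons related to those outcomes. The 12-month comparison then leans on a missing-at-random assumption that this event makes doubtful. Outcomes that were not collected cannot be recovered at the analysis stage.

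**Working it through.** **1. The plan's own attrition figure.** Sample size {14} gives a required n of 251, attrition of about 15% and 300 triads enrolled.
- 251 / (1 − 0.15) = 295.3, rounded up to 296. The stated 300 is consistent with this.
- 300 × 0.85 = 255, which is 4 above 251. The largest loss that keeps 251 is 49 triads, and 49/300 = 16.3%.
- If discontinuations under {11b} are not already counted in the 15%, more than 4 of them take the evaluable number below 251.

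**2. The texts side by side, for a woman who leaves but can be reached.**
- {11b}, first sentence: her situation is a listed reason for discontinuation.
- {11b}, second sentence: she is not lost to follow-up.
- {13}: she is due every remaining assessment.
- {20a}: she belongs in the 12-month analysis.
- Exclusion criteria, if she is pregnant and staying with her parents: she continues. Section {11b} neither covers nor exempts a temporary stay.

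**3. Size of a possible bias in complete cases.** The documents give no rates of separation or relocation, so every f and q below is an assumption. Let p be the true prevalence of PHQ-9 above 9 in an arm, f the fraction no longer assessed, and q the prevalence among those women. Then:

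observed prevalence = (p − f·q) / (1 − f)

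*True 40% (EUC) vs 25% (MILAP), difference 15 points.* The 40% is from {14}. The 25% is an assumption that departs from the 5–10% stated there. It is near the value implied by the mediation inputs in {14}: R² = 0.13 with 1:1 allocation gives a mediator shift of 2·√0.13 = 0.72 SD; the total odds ratio is about 0.77 × 0.5^0.72 = 0.47; the odds are 0.667 × 0.467 = 0.311; the prevalence is about 24%.
- (A) f = 10%/3%, q = 70%/30%: (0.40 − 0.070)/0.90 = 0.367; (0.25 − 0.009)/0.97 = 0.248; difference 11.8 points.
- (B) f = 10%/3%, q = 10%/10%: (0.40 − 0.010)/0.90 = 0.433; (0.25 − 0.003)/0.97 = 0.255; difference 17.9 points.
- (C) f = 15%/5%, q = 70%/30%: (0.40 − 0.105)/0.85 = 0.347; (0.25 − 0.015)/0.95 = 0.247; difference 10.0 points.

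*True 40% vs 10%, difference 30 points (upper end of the 5–10% in {14}).* The EUC values are unchanged. MILAP becomes:
- (A) (0.10 − 0.009)/0.97 = 0.094; difference 27.3 points.
- (B) (0.10 − 0.003)/0.97 = 0.100; difference 33.3 points.
- (C) (0.10 − 0.015)/0.95 = 0.089; difference 25.8 points.

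*No true effect, 40% in both arms.*
- f = 20%/10%: with q = 10%, 0.475 − 0.433 = 4.2 points of false benefit; with q = 40%, zero; with q = 90%, 0.275 − 0.344 = 6.9 points of false harm.
- f = 5%/2%: from 1.0 point of false benefit (q = 10%) to 1.6 points of false harm (q = 90%).

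**4. Bounds with no assumption about the missing women.** With 15% missing in each arm and observed rates of 40% and 10%, the difference for all randomised women is 0.85 × 30 ± 15, that is 10.5 to 40.5 points.

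**5. Power.** For 40% vs 10%, power stays above 99.9% even with 30% loss (two-sided 5% assumed, since the article states no alpha). For the direct effect on depression the problem is bias and not power.

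**The case against.** The opposing case has real force.

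- *The wording can be read benignly.* Relocation and separation may be meant only as reasons why contact fails, with the contact sequence as the actual test. The heading refers to interventions, {13} plans assessments for all, {18b} holds them where participants prefer, and {11c} keeps contact details current. This reading is available, so the loss of follow-up in reachable women is a risk from ambiguity and not a stated rule. The ambiguity stands, because nothing says these women will be assessed.
- *A reader might infer that outcome data are removed or that intention-to-treat is broken.* The documents do not support either. Nothing says that collected data are deleted; at most, later assessments are not made. The analysis is not confined to women still living with husband and mother-in-law, because imputation or full information maximum likelihood is planned and earlier visits enter the longitudinal model. Those methods still assume missing at random, so the analysis is weakened.
- *Dependence on arm is inferred.* Support for leaving is listed under EUC only for women who ask for it, entrants want to stay in the relationship, shelter is open to both arms, and {11d} prohibits no care. A difference between arms is plausible but not documented.
- *The pregnancy clash is conditional.* A temporary stay with parents need not mean that the triad has stopped living together. The two sections conflict only if staff read it that way.
- *The 15-point example flatters the concern.* With 40% vs 10% the relative distortion is 9–14%, against 19–33% with 40% vs 25%, and the trial's conclusion would be unlikely to change. This stands, which is why both sets are shown.

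**Conclusion.** The concern holds in a limited form. Section {11b} gives two incompatible tests, and one of them lets staff stop assessing a reachable woman after an event linked to violence and to services the trial offers. That undercuts {13} and the 12-month analysis in {20a}, and the methods in {20c} may not repair it if leaving depends on violence or distress arising after the last completed visit.

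The size cannot be derived from the documents. Under the assumed rates, complete cases would show a true 15-point difference as 10.0 to 17.9 points and a true 30-point difference as 25.8 to 33.3 points, so the bias can go either way. Imputation using earlier visits could reduce this by an amount that cannot be stated. No comparable figure can be given for IPV, because the article gives no expected IFVCS values. The documents do not support the stronger inferences of deleted data, a broken intention-to-treat analysis, a demonstrated difference in leaving between arms, or an outright contradiction with the pregnancy rule.

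**What to change.** Amend {11b} to separate the end of the intervention from the end of outcome assessment:

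- State that women who relocate, separate or stay elsewhere remain in the trial and are assessed at all remaining visits, in person or by phone as safety allows, with household status recorded each time.
- Limit loss to follow-up to withdrawal of consent to assessment or failure of the contact sequence already described in {11b}.
- Reconcile {11b} with the exclusion criteria on temporary moves during pregnancy. How remaining sessions are handled for such women is for the clinical team.

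A sensitivity analysis for departures from missing at random would be a useful addition. That and the imputation details may properly sit in the statistical analysis plan, and their absence from the article is not part of this point.

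The cost is a protocol amendment and some phone or travel expense for women who have moved. No additional triads are needed. Recruitment is expected to run to March 2027 (Trial status), so an amendment can still protect much of the follow-up.
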